# Standing up in multiple sclerosis (SUMS): protocol for a multi-centre randomised controlled trial evaluating the clinical and cost effectiveness of a home-based self-management standing frame programme in people with progressive multiple sclerosis

**DOI:** 10.1186/s12883-016-0581-8

**Published:** 2016-05-05

**Keywords:** Progressive Multiple Sclerosis, Standing, Standing frame, Physiotherapy, Self-management, Cost effectiveness, Mobility

## Abstract

**Background:**

Multiple sclerosis (MS) is an incurable, unpredictable but typically progressive neurological condition. It is the most common cause of neurological disability in young adults. Within 15 years of diagnosis, approximately 50 % of affected people are unable to walk unaided, and over time an estimated 25 % depend on a wheelchair. Typically, people with such limited mobility are excluded from clinical trials. Severely impaired people with MS spend much of their day sitting, often with limited ability to change position. In response, secondary complications can occur including: muscle wasting, pain, reduced skin integrity, spasms, limb stiffness, constipation, and associated psychosocial problems such as depression and lowered self-esteem. Effective self-management strategies, which can be implemented relatively easily and cheaply within people’s homes, are needed to improve or maintain mobility and reduce sedentary behaviour. However this is challenging, particularly in the latter stages of disease. Regular supported standing using standing frames is one potential option.

**Methods/Design:**

SUMS is a pragmatic multi-centre randomised controlled trial evaluating use of Oswestry standing frames with blinded outcome assessment and full economic evaluation. Participants will be randomly allocated (1:1) to either a home-based, self-management standing programme (with advice and support) along with their usual care or to usual care alone. Those in the intervention group will be asked to stand for a minimum of 30 min three times weekly over 20 weeks. Each participant will be followed-up at 20 and 36 weeks post baseline. The primary clinical outcome is motor function, assessed using the Amended Motor Club Assessment. The primary economic endpoint is quality-adjusted life years. The secondary outcomes include measures of explanatory physical impairments, key clinical outcomes, and health–related quality of life. An embedded qualitative component will explore participant’s and carer’s experiences of the standing programme.

**Discussion:**

This is the first large scale multi-centre trial to assess the clinical and cost effectiveness of a home based standing frame programme for people who are severely impaired by MS. If demonstrated to be effective and cost-effective, we will use this evidence to develop recommendations for a health service delivery model which could be implemented across the United Kingdom.

**Trial registration:**

ISRCTN69614598

**Date of registration:**

3.2.16 (retrospectively registered)

## Background

Multiple sclerosis (MS) is an incurable, unpredictable but typically progressive, life-long, neurological condition, affecting approximately 100,000 people in the United Kingdom (UK) [1]. It is the most common cause of neurological disability in young adults, with an estimated cost of £1.4 billion/annum to the National Health Service (NHS) and society [2]. Although most people start with a relapsing-remitting disease course, approximately two-thirds move to a progressive phase within eight years, at which point medical interventions are limited. Within 15 years of diagnosis, an estimated 50 % of affected people are unable to walk unaided, and over time 25 % become dependent on a wheelchair [3]. It is, therefore, unsurprising that mobility is a major concern for people with MS and health professionals. Surveys of people with MS consistently rank mobility as their highest priority [4, 5] and most important yet most challenging daily function [6]. Mobility has been correlated negatively with employment status and quality of life [2]. Evidence shows that enhancing physical activity and reducing sedentary behaviour can improve mobility and directly associated complications [7], providing a persuasive argument for ensuring that optimal physical management is a clinical priority.

NICE Guidelines emphasise that mobility spans much more than simply walking [7], including activities necessary for daily functioning: the ability to stand, safely transfer from wheelchair to toilet or to bed, and to move in bed. People with MS who are severely impaired spend much of their day sitting, often with limited ability to change position. In response, secondary complications can occur rapidly, including muscle wasting, pain, reduced skin integrity, spasms, limb stiffness, constipation, and associated psychosocial problems such as depression and lowered self-esteem [8]. These secondary problems can accelerate the loss of independence in daily function, and can impact negatively upon quality of life [4, 9] and self-identity. The clinical significance of these issues is underlined by their consistent prominence in policy documents for long-term neurological conditions [7, 10].

There are also significant economic costs related to increasing immobility and secondary complications since they increase the burden of care, delay rehabilitation and increase healthcare costs. It is estimated that approximately 15 % of people with MS will, at some point in time, develop a pressure sore [11], with treatment costs of a single pressure sore ranging from £1,064 to £24,214 [6]. The mean cost per wheelchair dependent patient is 4–5 times higher than an ambulatory patient [12]. This clearly has significant implications to the health services.

Evidence from studies of a range of neurological conditions, including MS, shows that increasing physical activity by interventions such as physiotherapy, can improve balance and mobility and reduce associated secondary health problems which arise from immobility [7]. However, increasing physical activity is difficult when disability is severe. Physiotherapy typically comprises short intermittent episodes of face-to-face sessions. On-going physiotherapy is rarely possible due to resource restrictions [13, 14]. While group-based exercise programmes are becoming more common, they can be inaccessible, and may have inappropriate content, for people with severe impairments [15]. Effective self-management strategies, which can be implemented relatively easily and cheaply within people’s homes, are needed for severely impaired individuals to improve or maintain their ability to move and reduce their sedentary behaviour. However this is challenging, particularly in the latter stages of disease. Regular supported standing using standing frames is one potential self-management option.

A systematic review investigating effectiveness of supported standing in neurological conditions [8], provided some data to support its acceptability, feasibility and efficacy but highlighted that more robust evidence is required. Of 17 randomised controlled trials (RCTs), only two were of high quality, and only one trial involved people with MS [16], which was a short-term, hospital based programme. Our updated literature search additionally identified one mixed-methods study [17] and a qualitative study [18], but no further RCT’s investigating this aspect of MS rehabilitation management.

Among the work of this research team, a study be [name] et al., has provided compelling evidence of the need for a trial of a managed standing frame programme. This study used a mixed-methods approach involving nine in-depth single case studies [17] to provide an in-depth understanding of the experiences of people with MS who participated in the standing programme. Over the course of a year, in addition to a range of objective measures, [name] undertook 27 in-depth interviews. Respondents’ stories reveal how the programme enabled them to “reconnect with their body”, “regain lost skills”, and gain a sense of “being in control”. In line with other related research [18] these interviews provided convincing qualitative evidence that this self-management standing programme reinstated a sense of belonging and optimism about the future by restoring important life roles and feelings of normality. A particularly debilitating secondary complication of immobility is stiff/hypertonic muscles. Our laboratory-based studies [19] determined that the duration and magnitude of force required to ease the stiffness in hypertonic lower limb muscles could only be achieved in a supported standing position for more severely impaired people with MS.

The proposed study builds on these existing research strands, asking the question “What is the clinical and cost effectiveness of a home-based self-management standing frame programme in people who are severely impaired with progressive MS?” The aim of this definitive multi-centre randomised controlled study is to investigate the clinical and cost effectiveness of a home-based supported standing programme for people severely impaired with progressive MS.

More specifically, the objectives are to:Assess the clinical effectiveness of the standing frame programme in improving motor function (primary outcome).Assess the clinical effectiveness of the standing frame programme in improving balance, muscle strength, joint and muscle range, painful spasms, respiratory, bladder and bowel function, number of falls and quality of life (secondary outcomes).Establish the cost-effectiveness of the standing frame programme versus usual care.Explore the subjective experience of using a standing frame within the home, from the perspective of both the person with MS and their carer.

## Methods

### Trial design

This is a pragmatic multi-centre randomised controlled trial with blinded outcome assessment and full economic evaluation. Figure 1 shows the participant pathway.

**Fig. 1 Fig1:**
[figure not shown]
Trial flow chart of participant pathway

### Study Setting

Eight healthcare sites will be involved in this multi-centred RCT which is based in two geographical regions of England: Devon/Cornwall and East Anglia. Each site consists of up to seven individual community based therapy teams.

### Participants

#### Sample size

Our primary outcome is the Amended Motor Club Assessment (AMCA) at 16 weeks follow-up. Our primary analysis will utilise analysis of covariance (ANCOVA), comparing AMCA scores at week 36 between allocated groups, adjusting for baseline AMCA score. The trial is powered to detect a between-group difference of nine points which is both plausible and considered clinically relevant [17, 20]. In people with severe MS a score change of 9 points is considered clinically significant, reflecting changes such as allowing a person to balance and lean forwards in sitting to dress themselves or to stand in the shower and wash their hair with two hands.

Estimates of final SD and baseline/follow-up correlation for AMCA are subject to uncertainty and thus we have used conservative 80 % upper confidence limits for both parameters in our calculations. To detect a between-group difference of nine points, with 80 % power and at the 5 % significance level, requires data from 55 participants per group [21].

Allowance is required for people not completing the programme, and for participants not attending the final follow-up assessment. Based on our previous experiences, we have allowed for 20 % loss to follow-up. Therefore the sample size required is 69 participants per group, rounded to a total of 140. An estimated 380 people will need to be screened to achieve the required sample size.

### Inclusion criteria

The study population will comprise individuals diagnosed with primary or secondary progressive MS according to McDonald’s criteria [22].

These participants will:be aged >18 yearsbe willing and able to consent to participatescore 6.5–8.0 on the Expanded Disability Status Scale (EDSS), i.e. people who “require bilateral assistance to walk 20 metres or less” to those “restricted to bed or wheelchair”be able to get into a standing frame independently or with assistance from one personhave the agreement of another person (e.g. carer) should assistance be necessary for the standing programmebe able and willing to accommodate the standing frame in their homebe willing and able to travel to local assessment centres for blinded outcomes assessment

### Exclusion criteria

Participants will be excluded if they:have had any recent changes in disease modifying therapies. More specifically they will be excluded if: they have ever had Alemtuzumab, are within past six months of ceasing Nataluzimab, or are within three months of ceasing any other MS disease modifying drughave relapsed/received steroid treatment within the last monthare currently undertaking a regular standing frame programme (>x1/week), or have done so during the past six monthshave a history of osteoporotic-related fractureshave co-morbidities which contraindicate standing in the frame (e.g. foot ulceration, uncontrolled epilepsy) or likely to impact on the trial (e.g. chronic jaundice, heart disease, age related multiple co-morbidities)currently participating in another clinical trial (rehabilitation or pharmacological)

Identification and recruitment of participants will be via a number of routes which include screening MS databases, identification by healthcare professionals, and advertising via MS support groups and newsletters.

### Randomisation

Participants will be randomised immediately after the baseline assessment. Randomisation, using random sized permuted blocks, will be on a 1:1 basis to receive the intervention plus usual care or usual care only. It will be stratified by region and baseline EDSS (≤7.0 or ≥7.5). The allocation sequence is computer-generated by the local United Kingdom Clinical Research Collaboration Registered Peninsula Clinical Trials Unit (UKCRC PenCTU) (Registration Number 31) in conjunction with an independent statistician who will have no involvement with the final analysis. Following assessment, the blinded assessor will input the details of the participants directly into the randomisation web-site. This will generate an e-mail stating the participant’s allocated treatment group to the regional study co-ordinators and study administrator to notify them of the treatment allocation.

### Blinding

The trial participants and carers are unable to be blinded in this trial due to the nature of the intervention. Similarly, the treating physiotherapists and health care providers are unable to be blinded. However, the outcome assessors will be blinded to participants’ allocated group. All assessments will be undertaken in separate visits independently of delivery of treatment/usual care and away from the participant’s home. Every effort will be made throughout the trial to ensure these assessments are blinded. Upon any interaction with the participant, the blinded assessors will remind participants not to discuss their allocated group, and this will be re-iterated within any written and telephone correspondence.

At each assessment time point, the blinded assessor will be asked to record on a standardised form whether or not they were un-blinded to the group allocation, and if so the reasons for this.

### Interventions

Participants in the intervention group will be asked to stand in an Oswestry standing frame [17] for 30 min three times per week for a total of 16 weeks during a 20 week period. The Oswestry standing frame is a wooden frame, used in clinical practice, which provides support in standing whilst allowing for exercise and controlled movement.

The treating physiotherapist will teach the participant and carer safe and effective use of the standing frame over two face-to-face sessions in the participant’s home (~60 min/session). Participants will also be taught exercises and stretches to undertake in the frame. A detailed user-friendly information leaflet and digital versatile disc (DVD) will be provided to support these sessions. Further support will be provided by weekly telephone contact for four weeks, and then monthly for two months. Telephone calls will focus on facilitating individuals to set and achieve personal targets.

### Standardisation and fidelity of the intervention

Treating physiotherapists from each of the eight healthcare sites will perform the interventions as part of their NHS role; all physiotherapists will implement the intervention in a similar manner.

Use of standing frames is incorporated within undergraduate physiotherapy training and is a recognised core skill for neurological physiotherapists. To standardise and optimise implementation of the intervention, treating therapists, participants and carers will be provided with an information pack. This includes a written template of what is required to be undertaken within each session and a link to the study web-site, which houses a range of resources including a detailed booklet, instructional video with suggested exercise/stretches/balance activities, and evidence based articles on this topic.

All treating therapists will be required to complete a pre-formatted checklist to self-assess their fidelity with the content of the sessions. They will be asked to record any deviations from the protocol on a Protocol Deviations form. In addition, 10 % of the intervention sessions will be assessed in each region by the unblinded regional Principal Investigator who will observe the home-based treatment sessions and independently complete the same fidelity checklist.

### Usual care

This trial will use a usual clinical care control group. A recent MS Society national survey demonstrated that access to physiotherapy services varies throughout the UK/England [14]. Although usual care varies between individuals [1], it rarely involves regular physiotherapy intervention either within the community or hospital [13]. Any intervention is generally limited to a few visits, typically reacting to presenting problems (e.g. practising transfer skills, providing mobility aids) rather than promoting long-term preventative self-management [13]. This national picture reflects the care provided in our study regions. The usual care received (including frequency of physiotherapy intervention as well as any other health/social service interventions and medications) will be recorded within the economic cost effectiveness assessments.

### Data collection and outcome measurements

Standardised, validated clinician-rated and patient self-reported clinical outcomes will be measured at baseline, immediately post intervention (20 weeks) and follow-up (week 36). Any deviations from this will be recorded on a Protocol Deviations form. The longer term follow-up is important to assess maintenance of any observed effect, and determine whether long-term engagement is sustained once support from the treating physiotherapist is withdrawn.

Measures have been selected on the basis of demonstrated reliability and validity in assessing physical impairments, clinical outcomes, quality of life, and economic costs in people with MS.

### Primary outcome measures

The primary clinical outcome is motor function, assessed using the Amended Motor Club Assessment (AMCA) [23]. This rates motor impairment of the lower limb and trunk and key functional movements such as sit-to-stand and standing balance. It was developed specifically for people with MS and has demonstrated validity, reliability and responsiveness [20, 23, 24]

The primary economic endpoint is the quality-adjusted life year (QALY), assessed using the EuroQol five dimensional descriptive system, the EQ-5D-5 L self report measure [25].

### Secondary outcome measures

A. Key clinical outcomes:Bowel and bladder control using the self-report Bladder and Bowel Control Scales [26]Sitting balance using the single item Modified Functional Reach in Sitting [27]Falls frequency through a single yes/no question “Did you fall today?”, recorded on the daily diaryHealth-related quality-of-life (HRQoL), using the 29 item Multiple Sclerosis Impact Scale (MSIS-29 version 2.0) [28], a disease specific patient-reported outcome measure with a preference-based tariff [29] for use in sensitivity analyses for the Quality Adjusted Life Year (QALY) outcome.

B. Explanatory physical impairments:Knee extensor strength using a portable hand-held dynamometer [30]Length of hip flexors, hamstrings and ankle plantarflexors using manual goniometry [16]Spasm frequency using the Penn Spasm Frequency Scale [31]Respiratory capacity using a hand-held spirometer to record forced expiratory volume at one second [32]

### Measures of intervention adherence

A simple pre-formatted daily diary will be completed by those allocated to the standing frame programme. Either the participant or carer will record adherence with the intervention (frequency, duration, reasons for not standing), and will also have the opportunity to comment on why standing was continued or stopped. Adverse events (including new symptoms and falls) will also be recorded in the diary.

The usual care group will also be asked to complete a daily diary to capture adverse events (including new symptoms and falls).

### Safety monitoring

Participants will be monitored for adverse events via completion of their study daily diaries and during follow-up assessments. The group receiving the intervention will also be monitored during the scheduled telephone calls with their treating physiotherapist. Physiotherapists will be asked to report all adverse events to the research team, whether or not they are thought to be related to the intervention.

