### Statistical analysis

A full statistical analysis plan will be developed and approved by an independent statistician, prior to final database-lock. The primary statistical analysis will utilise analysis of covariance (ANCOVA), comparing AMCA scores at week 36 between allocated groups, adjusting for baseline AMCA score and the two stratification variables (baseline EDSS category and geographical region). The primary comparative analyses of all outcome measures will be on the basis of intention-to-treat (adverse events will be presented per protocol if different). Between-group differences will be presented with 95 % confidence intervals wherever possible, with the significance level for hypothesis testing set at 5 %, unless otherwise stated.

Secondary outcomes will be compared between groups in a similar way to that for the primary outcome. Comparisons of interest will be presented with 95 % confidence intervals for both unadjusted and adjusted between-group comparisons.

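### Adverse events are also sought at six physiotherapist calls in the intervention arm only, so counts by arm that pool all sources are at risk of ascertainment bias

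*Protocol article*

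**What the plan says.** The Safety monitoring section first describes what applies to everyone: "Participants will be monitored for adverse events via completion of their study daily diaries and during follow-up assessments". The diaries are matched on this point. In the section on measures of intervention adherence, the standing arm's diary carries harms as well as adherence: "Adverse events (including new symptoms and falls) will also be recorded in the diary". For the other arm: "The usual care group will also be asked to complete a daily diary to capture adverse events (including new symptoms and falls". The data collection section places the assessments at weeks 20 and 36 in both arms.

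Safety monitoring then adds a channel for one arm: "The group receiving the intervention will also be monitored during the scheduled telephone calls with their treating physiotherapist". The Interventions section sets the number of calls: "Further support will be provided by weekly telephone contact for four weeks, and then monthly for two months". Nothing equivalent is described for usual care. The reporting duty is broad: "Physiotherapists will be asked to report all adverse events to the research team", whether or not an event is thought to be related.

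On analysis, the Statistical analysis section says little. A parenthesis in its sentence on intention-to-treat comparisons states that "adverse events will be presented per protocol if different". Falls are handled elsewhere. They are a secondary outcome, taken from a yes/no question in the daily diary, and secondary outcomes are to be compared between groups.

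**The concern.** If one arm has an extra occasion for events to come to light, it can show more events with no true difference in harm. Three features of this trial make that worth attention.

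- The calls are made by the treating physiotherapists, who by the Blinding section know the allocation.
- The calls fall early. They overlap the period of up to four weeks that the Discussion allows for becoming re-accustomed to standing. A true early excess with standing and an excess due to detection would appear together and be hard to separate.
- New symptoms count as adverse events. It is an inference, but a reasonable one, that minor symptoms may go unwritten in a diary and still be mentioned in a call.

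At stake is how the harms table is read. The programme could seem to cause more events than it does. The primary outcome, the sample size and the type I error rate are not touched.

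**Working it through.** The plan gives no figure to reproduce, so the check sets the channels side by side and then asks how large the effect could be.

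**Channels named for adverse events**

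| Channel | Standing frame arm | Usual care arm |
|---|---|---|
| Daily diary | yes | yes |
| Assessments at weeks 20 and 36 | 2 | 2 |
| Scheduled physiotherapist calls | 4 + 2 = 6 | 0 |

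Four weeks of weekly calls and two months of monthly calls end at about week 12, if support starts near baseline. That is 12/36 = 1/3 of follow-up.

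**Possible size.** Let the true event rates be equal. Let s be the share of events caught by the common channels, c the share of missed events that the calls recover, and w the share of events that fall in the period covered by calls. The ratio of recorded events, intervention to control, is

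ratio = [s + w(1 − s)c] / s = 1 + w(1 − s)c / s.

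The documents give none of s, c and w, so all three are assumptions. Setting w = 1 gives the ratio within the call period. Setting w = 1/3 gives it over 36 weeks with events spread evenly.

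| s | c | Call period (w = 1) | All 36 weeks (w = 1/3) |
|---|---|---|---|
| 1.0 | any | 1.00 | 1.00 |
| any | 0 | 1.00 | 1.00 |
| 0.9 | 0.25 | 0.925/0.9 = 1.03 | 1.01 |
| 0.8 | 0.5 | 0.90/0.8 = 1.13 | 1.04 |
| 0.7 | 0.5 | 0.85/0.7 = 1.21 | 1.07 |
| 0.6 | 0.5 | 0.80/0.6 = 1.33 | 0.667/0.6 = 1.11 |
| 0.5 | 0.5 | 0.75/0.5 = 1.50 | 0.583/0.5 = 1.17 |

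The top of the range is not a bound. It depends on where the assumptions stop: with s = 0.5, c = 0.75 would give 1.75 in the call period. If events cluster in the first weeks, w exceeds 1/3 and the 36-week ratio moves towards the call-period column.

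**Falls outcome.** Its only stated source is the diary, which both arms keep. The calls do not enter it, so this mechanism leaves its ratio at 1.00.

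**The case against.** The strongest reply is that asking about harms during calls that belong to the intervention is ordinary safety oversight, and that the article never says how sources will be combined. The statistical analysis plan is not shown and may settle it. The first part stands: the extra surveillance is not an error, and nothing here asks for its removal. The second part stands only in part. The unequal channels are fixed by the protocol text itself, and adverse events are mentioned within the sentence on comparative analyses. Any display by arm that uses all sources therefore inherits the inequality, with or without a test.

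A reader might infer more than the documents support:

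- **That the two home teaching sessions are also a capture channel, giving eight extra contacts.** Safety monitoring names only the calls. The sessions enter by implication, through the physiotherapists' general reporting duty. The stated difference is six.
- **That a formal between-group comparison of adverse events is planned and is biased.** The text says events will be presented and names no test. The risk applies to counts pooled over sources.
- **That the control arm merely self-reports while the intervention arm is actively questioned.** Both arms are monitored at the assessments, and the Interventions section describes the calls as focused on personal targets.
- **That the falls comparison is compromised.** As specified, it is diary-based in both arms.
- **That the safety results could not be read in either direction.** Extra detection in the treated arm can only raise that arm's count. It could create or enlarge an apparent excess, but it could not hide harm through lower detection in that arm.

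**Conclusion.** The point holds in a limited form. Capture of adverse events is unequal by design: six calls in one arm and none in the other, in about the first third of follow-up. Counts by arm that pool all sources are at risk of bias towards more events in the intervention arm. The direction is clear, unless the diaries and assessments miss nothing or the calls recover nothing, in which case there is no effect.

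The size cannot be set from the documents. For s from 0.5 to 1.0 and c up to 0.5, the spurious ratio runs from 1.00 to about 1.5 within the call period, and from 1.00 to about 1.17 over 36 weeks with events spread evenly. These figures illustrate the mechanism and do not estimate it. The change is a cheap improvement to how harms are presented. It does not repair a fault in the main analysis.

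**What to change.** 1. Record on the adverse event form every source from which each event is known (diary, week 20 or week 36 assessment, physiotherapist contact), and not only the first. An event that was both written in the diary and mentioned in a call then stays in the comparison.
2. State in the analysis plan that adverse events are presented by arm on the channels common to both: diaries and the two assessments.
3. List events known only from physiotherapist contacts separately for the intervention arm, and keep them in full safety oversight, including the updates to the steering committee chair.
4. Keep the falls outcome diary-only, so that falls reported in calls do not enter it.

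The cost is one form field and a sentence or two in the analysis plan. The comparative table will show fewer intervention-arm events, but none is lost from oversight. One limit remains: if calls prompt participants to fill in the diary, or to leave events out of it because they have already told the physiotherapist, restricting the sources does not remove that. The source field is best added early, because source may be hard to recover later. The article reports 49 participants recruited against a target of 140.
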